##### Social and interpersonal functioning

The Inventory of Interpersonal Problems (IIP-64) is used to assess interpersonal problems [56]. It is a self-report measure consisting of 64 items assessing eight dimensions of interpersonal problems: (1) domineering/controlling (e.g., “It is hard for me to take instructions from people who have authority over me”), (2) vindictive/self-centred (“It is hard for me to trust other people”), (3) cold/distant (“It is hard for me to show affection to others”), (4) socially inhibited (“It is hard for me to introduce myself to someone”), (5) non-assertive (“It is hard for me to be firm when I need to be”), (6) overly accommodating (“It is hard for me to be angry at others”), (7) self-sacrificing (“It is hard for me to be angry at someone I like”) and (8) intrusive/needy (“It is hard for me to be on my own”). Respondents are asked to consider each problem and to rate how distressing that problem has been on a scale ranging from 0 (not at all) to 4 (extremely). The IIP-64 possesses good psychometric properties, with Cronbach’s α of .96 for the total score and a test-retest reliability coefficient of .78 [57].

##### Personality functioning

Personality functioning is assessed with the Severity Indices of Personality Problems – Short Form (SIPP-SF) and the Dimensional Assessment of Personality Pathology – Short Form (DAPP-SF).

The SIPP-SF [58] is a dimensional self-report measure assessing the severity of personality pathology and has been developed for research purposes. The SIPP-SF aims to assess the core components of adaptive and maladaptive personality functioning. It consists of 60 items, which cluster into five higher-order domains: (1) self-control, (2) identity integration, (3) relational capacities, (4) social concordance and (5) responsibility [59]. The SIPP-SF asks respondents to think about the past 3 months and to answer the extent to which they agree with statements such as “I frequently say things I regret later”. Items are rated on a four-point Likert type scale ranging from 1 (fully disagree) to 4 (fully agree). High scores on the domains indicate better functioning. The SIPP-SF is a shortened version of the SIPP-118, which has good reliability (Cronbach’s α ranging from .62 to .89, M = .78) [59].

The DAPP-SF consists of 136 of the original 290 items of the DAPP-BQ [60,61]. The 136 items cover 18 personality disorder trait-based dimensions fitting into four broad higher order factors: emotional dysregulation, dissocial behaviour, inhibition and compulsivity [62]. The items are rated on a five-point Likert scale with scores ranging from 1 (very unlike me) to 5 (very like me). Both the DAPP-BQ and the DAPP-SF have good psychometric features [62].

##### Attachment and mentalizing

Attachment is assessed with the Experiences in Close Relationships (ECR) questionnaire [63,64] and the Dutch Attachment Style Questionnaire [65]. Mentalizing is measured using the Reflective Functioning Questionnaire (RFQ).

The ECR questionnaire [63,64] measures adult attachment in romantic relationships. It contains two subscales, Anxiety about rejection and abandonment (e.g., “I worry about being abandoned”) and Avoidance of intimacy (“I feel very uncomfortable when my partner wants to have a close connection to me”), both consisting of 18 items. Individuals are asked to rate each statement on a seven-point Likert scale ranging from 1 (disagree strongly) to 7 (agree strongly).

The Dutch Attachment Style Questionnaire [65] is a measure of attachment to others in general (and thus not to a specific person as is the case for the ECR). The questionnaire consists of 24 items and measures the following four attachment styles defined by Bartholomew and Horowitz [66]: (1) secure attachment, consisting of eight items (e.g., “I trust others to be there when I need them”), (2) avoidant attachment, consisting of five items (e.g., “It is important for me to be independent”), (3) preoccupied attachment, consisting of seven items (e.g., “I have the feeling that most of the time I like others better than they like me”) and (4) anxious attachment style, consisting of four items (e.g., “I am afraid that others will betray me when I become too close to them”). All items are scored on a five-point Likert scale ranging from 1 (strongly disagree) to 5 (strongly agree). The internal consistency ranges from .61 (Avoidant) to .86 (Preoccupied) [65].

The RFQ [67] consists of 57 items with ratings on a seven-point scale (1 = Strongly disagree, 7 = Strongly agree). An example of a statement is “It costs me a lot of time to understand the thoughts and feelings of other people”. The internal consistency of the RFQ is good (α = .77) and the test-retest reliability is high (α = .78) [67].

##### Quality of life

Quality of life is measured using the EuroQol EQ-5D-3 L [68]. This self-report questionnaire provides a simple method to capture health problems according to a five-dimensional classification: mobility, self-care, usual activities, pain/discomfort and anxiety/depression. Each dimension is divided into three levels: no problem, moderate problems, extreme problems. The five dimensions can be summarized into a “value”, based on the preferences of the general public. These values can be used as societal weights for the calculation of quality-adjusted life years (QALYs) in health economic evaluations (see also below). To calculate these societal weights, we will use a Dutch validation study [69,70]. Next to the five dimensions, the EuroQol presents a vertical visual analogue scale, ranging from 0 (worst imaginable health) to 100 (best imaginable health). The values are seen as representing patients’ values, in contrary to the societal weight based on the five dimensions. The reliability of the EQ-5D-3 L has been investigated and found to be acceptable [71] and it has shown to be sensitive to change in patients with personality disorders [4,72].

##### Mental-health-related functional impairment

The Sheehan Disability Scale (SDS) [73] was developed to assess functional impairment in three inter-related domains: work/school, social and family life. It is a brief self-report tool consisting of four questions. The patient rates the extent to which work/school, social life and home life or family responsibilities are impaired by his or her symptoms on a 10-point visual analogue scale. An example question is: “I do not function well at work because of my problems”. The internal consistency of the SDS total score is good (Cronbach’s α = .89) and test-retest reliability for the SDS total score is acceptable (ICC = .73) [74].

##### DSM-IV Axis-I and Axis-II-diagnoses

The SCID-I [40,75] is used to diagnose Axis I disorders at intake and at 36 months follow-up. The SCID-II [38,76] is used for diagnosing Axis II personality disorders at intake and at 36 months follow-up. The interviewer is an MSc-level psychologist, who was trained by an expert trainer in the SCID-II. No interrater reliability data were collected in this study. Previous research has shown, however, that the SCID-II has good interrater reliability and test-retest interrater reliability in adults [77,78].

##### Patient adherence to the treatment

Patients’ adherence to the treatment is derived from the realized dose. The clinical staff record the type, number, and duration of all attended sessions and the number of missed sessions and reason for absence. Based on this information, we will calculate the proportion of missed sessions as a quantitative index of treatment adherence.

##### Costs

The intervention costs of MBT-DH and TAU are calculated using a mixture of top-down and bottom-up approaches. The intervention costs estimates will include personnel costs, implementation costs (e.g., hosting and coaching) and any other overhead costs associated with the treatment. Medical costs beyond the intervention costs of MBT-DH and TAU are calculated using the Trimbos and Institute for Medical Technology Assessment (iMTA) Questionnaire on Costs Associated with Psychiatric Illness (TiC-P: [79]). The TiC-P will be used to measure health care utilization at baseline and after 6, 12, 18, 24 and 36 months.

The first part of the TiC-P consists of questions on (1) the number of visits to, e.g., a general practitioner, psychiatrist (outside TAU or MBT-DH), medical specialist, physiotherapist or alternative health practitioner; (2) the day care/hospital lengths of stay (outside TAU or MBT-DH); and (3) the use of medication in the 4 weeks prior to filling out the questionnaire. These values are multiplied with unit prices of the corresponding health care services according to the Dutch manual for costing studies in health care [80]. The unit prices for 2010 will be adjusted to 2014 prices using the Consumer Price Index [81]. As the mean direct costs are measured per 4 weeks, we will multiply these values by 13 to estimate the annual costs.

The TiC-P also asks the patient to report any productivity losses, that is, absence from work or reduced productivity at work. This report is used to estimate the so-called “friction costs”: the monetary representation of the replacement of the labour. The friction-cost method takes the employer's perspective, and counts as lost only those hours not worked until another employee takes over the patient's work. This is a more conservative estimate than the so-called “human capital method”, which relates productivity costs one-to-one to the labour costs of the patient. The choice between friction costs and human capital is still a subject of debate among economists. In this study, we chose the more conservative friction-cost method [82].

### Questionnaires completed by therapists

Therapists complete questionnaires at 6, 12, 18, 24, 30 and 36 months after the start of treatment of each patient regarding treatment alliance, functional impairment of the patient, the Clinical Global Impression scale (CGI) and medication adherence.

#### Treatment alliance

The Helping Alliance Questionnaire (HAQ) is based on two types of “helping alliance”. Type I is about the experience of the therapist supporting and helping the patient. Type II is about the experience of joint collaboration [83]. Luborsky and colleagues expanded the original HAQ from 11 to 19 questions [84]. There is both a patient and a therapist version, but in this study only the therapist version is used. Items are rated on a six-point Likert scale (1 = I strongly feel it is not true; 6 = I strongly feel it is true). An example question is “My patient believes I’m experienced”. The total score is the mean of the item scores. The HAQ-II shows good internal consistency (α ranging from .90 to .93) [85] and test-retest reliability (.56) [84].

#### Functional impairment of the patient

We adapted the SDS [73] so that therapists can rate the functional impairment of the patient in three domains: work/school, social and family life.

#### Clinical global impression

The CGI [86] provides a summary of an individual’s clinical functioning as assessed by the therapist. The CGI consists of two ratings: Severity of Illness (CGI-S) at the moment of contact, and Global Improvement (CGI-I) of the patient since the start of treatment. Both use a seven-step categorical scale: for the CGI-S, ranging from 0 (normal, not at all ill) to 7 (among the most extremely ill patients), and for the CGI-I, from 0 (very much improved) to 7 (very much worse).

### Sample size and power calculation

Based on records of 2008, we estimated the number of new referrals per year to Arkin and De Viersprong. On average, the total annual number of new referrals was 265 at De Viersprong and 230 at Arkin. Out of all newly referred patients, 154 suffered from a severe BPD and met the inclusion criteria for this study. Assuming a refusal rate of 35%, this means that on average 8.1 patients could be included each month. Therefore, we expected to be able to recruit and assess 108 patients (54 in each arm) during a recruitment window of 14 months. Figure 1 shows the expected flow of participants from recruitment through the beginning of the study.

In this study the primary clinical outcome variable is the total score on the BPDSI, an index of the severity of BPD manifestations. Bales and colleagues [35] found a large effect size of 1.23 on the BPDSI after 18 months of MBT-DH, in a sample of 45 BPD patients. Although Bateman and Fonagy [33] used another index for the severity of borderline symptoms (the Zanarini Rating Scale for Borderline Personality Disorder, a clinician-administered scale for the assessment of change in DSM-IV borderline psychopathology [87]), they also found a large effect size 5 years after MBT (a difference of 64% between TAU [mean = 15.1, SD = 5.3) and MBT-DH [mean = 5.5, SD = 5.2; effect size = 1.8]). Although within-group effect sizes for MBT can be expected to be large, the specialist TAU investigated in the present study may be more effective than TAU provided in the UK. Yet, given differences in effect sizes in previous trials, particularly in the long term, we expect MBT-DH patients to improve at least 20% more than TAU patients on the BPDSI at 18 months after the start of the intervention. With a sample of 54 patients per group, an effect size of at least .65 on the BPDSI could be detected with a power of 92% (α = .05, *β =* .083), which reflects a reasonable, realistic and clinically relevant effect.

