**Methods/design:**

The trial is being conducted at two sites in The Netherlands. Patients with a DSM-IV-TR diagnosis of borderline personality disorder and a score of ≥ 20 on the Borderline Personality Disorder Severity Index were randomly allocated to MBT-DH or treatment as usual. The MBT-DH program consists of a maximum of 18 months’ intensive treatment, followed by a maximum of 18 months of maintenance therapy. Specialist treatment as usual is provided by the City Crisis Service in Amsterdam, a service that specializes in treating patients with personality disorders, offering manualized, non-MBT interventions including family interventions, Linehan training, social skills training, and pharmacotherapy, without a maximum time limit. Patients are assessed at baseline and subsequently every 6 months up to 36 months after the start of treatment. The primary outcome measure is the frequency and severity of manifestations of borderline personality disorder as assessed by the Borderline Personality Disorder Severity Index. Secondary outcome measures include parasuicidal behaviour, symptomatic distress, social and interpersonal functioning, personality functioning, attachment, capacity for mentalizing and quality of life. Cost-effectiveness is assessed in terms of the cost per quality-adjusted life year. Outcomes will be analyzed using multilevel analyses based on intention-to-treat principles.

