## Methods/design

### Design

This study is a multi-site RCT comparing the efficacy and cost-effectiveness of manualized MBT-DH and a manualized specialist TAU in the treatment of BPD. The inclusion of patients started in March 2009 and ended in July 2012. The last follow-up measurement, at 36 months, will be in July 2015. Two mental health care centres agreed to participate in this study: Arkin en De Viersprong, both located in Amsterdam. Arkin is a large mental health care centre that specializes in the treatment of BPD. De Viersprong is a national institute for personality problems, offering specialized outpatient, day hospital, and inpatient psychotherapy for adolescent and adult patients with severe personality problems and disorders. Arkin agreed to run four MBT-DH groups and De Viersprong agreed to run two MBT-DH groups in the context of the trial, each consisting of nine patients. The City Crisis Service, which is part of Arkin, agreed to run the specialist TAU condition. The overall aim was to randomize 54 patients to MBT-DH and 54 patients to TAU.

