### Procedure

All patients referred to one of the mental health care institutes were invited to attend an intake appointment. Patients who were deemed eligible received more information about the study and, if they were interested, a new appointment was set during which the BPSDI [39], and SCID-II [38] interviews were administered and other eligibility criteria were assessed. If patients met inclusion criteria, they provided informed consent and were randomized to either MBT or TAU by an independent researcher using a computerized 1:1 algorithm. Patients were subsequently asked to complete the baseline measures (see Figure 1). It was preferred that patients completed the measures in the clinic; however if patients insisted, they were allowed to complete questionnaires at home, in which case patients were asked to return the questionnaires within a week by regular mail.

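### The stated 92% power assumes 108 independent, fully observed patients; with MBT-DH given in six therapy groups and no allowance for loss by 18 months, it is optimistic

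*Protocol article*

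**What the plan says.** All references are to the Protocol article.

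- **Sample size and power calculation.** The text reads "With a sample of 54 patients per group, an effect size of at least .65" on the BPDSI is detectable with 92% power, with α = .05 and β = .083. The expected advantage on the BPDSI that leads to this figure is placed at 18 months. The section gives no ICC, design effect or post-randomisation loss rate. Its 35% is refusal before inclusion.
- **Design.** "The overall aim was to randomize 54 patients to MBT-DH and 54 patients to TAU". Arkin provides four MBT-DH groups, and "De Viersprong agreed to run two MBT-DH groups in the context of the trial, each consisting of nine patients". Six groups of nine make up exactly the 54 MBT-DH places.
- **Procedure.** Allocation is to individuals, "using a computerized 1:1 algorithm".
- **Treatments.** MBT-DH is a five-day-a-week programme over 18 months with daily group psychotherapy and further group components. TAU is mainly outpatient, with its intensity matched to the patient.
- **Statistical analyses.** Linear growth curve models are named for normally distributed outcomes. No therapy-group level is mentioned. The Abstract says "Outcomes will be analyzed using multilevel analyses based on intention-to-treat principles" without naming the levels.

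**The concern.** Patients who spend 18 months in the same therapy group share group dynamics and therapists, so their outcomes may be correlated. Here this arises mainly in one arm: patients are randomised individually, but the MBT-DH patients are then nested in groups (a partially nested design). Positive correlation raises the variance of the MBT-DH mean above that of 54 independent patients. Separately, a power figure that sets the number analysed equal to the number randomised holds only if every patient is assessed at 18 months.

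Two things are at stake. The first is how a null result would be read: a non-significant difference looks more conclusive at 92% power than at 75–85%. The second is the error rate of the primary comparison, should the groups be left out of the model.

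**Working it through.** **Inputs from the article.** n = 54 per arm; d = .65 (SD = 1); α = .05; 1:1 allocation; six MBT-DH groups of m = 9.

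**Assumptions, with no figure in the article.** ICC within MBT-DH groups 0–.10; loss by 18 months L = 0–20%, equal in both arms and across groups; groups stable at nine; TAU unclustered.

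**Step 1: reproduce the stated figure.** SE = √(1/54 + 1/54) = .1925; noncentrality = .65/.1925 = 3.38; 106 df. The two-sided noncentral t gives power 91.72%, so β = .083, as printed. A one-sided test gives 95.6% and does not match. The stated figure therefore contains no allowance for clustering or loss.

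**Step 2: loss alone.** With n = 54(1 − L), 20% loss leaves 43.2 per arm and power 84.8%.

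**Step 3: clustering in the MBT-DH arm.** The design effect is DE = 1 + (m − 1)·ICC, with m = 9(1 − L), and SE = √(DE/n + 1/n). Without loss, ICC .02, .05 and .10 give:
- DE = 1 + 8 × ICC = 1.16, 1.40 and 1.80;
- effective MBT-DH size 54/DE = 46.6, 38.6 and 30.0;
- SE larger by the factor √((DE + 1)/2) = 1.04, 1.10 and 1.18.

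Power by noncentral t on the effective sizes:

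| Loss by 18 months | ICC 0 | ICC .02 | ICC .05 | ICC .10 |
|---|---|---|---|---|
| 0% | 92% | 90% | 86% | 81% |
| 20% | 85% | 83% | 79% | 74% |

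**Step 4: degrees of freedom for six groups.** With a = DE/n and b = 1/n, Satterthwaite's formula is df = (a + b)² / (a²/5 + b²/(n − 1)). At ICC .10 without loss, a = .0333 and b = .0185, so df = 11.8 instead of 106. Power becomes:

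| Loss by 18 months | ICC .02 | ICC .05 | ICC .10 |
|---|---|---|---|
| 0% | 86% | 82% | 74% |
| 20% | 79% | 75% | 68% |

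**Step 5: type I error if groups are ignored.** For a comparison at one time point without loss, the true two-sided level is 2[1 − Φ(1.96/√((DE + 1)/2))]. This gives 5.9%, 7.4% and 9.8% at ICC .02, .05 and .10.

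**The case against.** **The model may already include the groups.** A reader might infer that the planned standard errors are too small. The article does not establish that. It calls the analysis multilevel without naming levels, the analysis section lists only model families, and a random-effects structure is commonly left to an analysis plan, which is not shown. Repeated measures within patients would also satisfy the word multilevel, so the wording settles nothing either way. This objection stands: the standard-error and type I error statements are conditional.

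**Follow-up runs to 36 months.** It is tempting to charge 36 months of attrition against the 92%. The expected difference behind that figure is placed at 18 months, so only loss by then bears on it directly.

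**The losses are overstated.** Step 2 treats a lost patient as contributing nothing. Growth models use partial records, the article describes telephone reminders and telephone interviews, and every patient has a BPDSI at eligibility. As an illustration, with an assumed baseline–outcome correlation r and d divided by √(1 − r²), the 79% at ICC .05 and 20% loss becomes 83% at r = .3 and 89% at r = .5. The 74% at ICC .10 becomes 78% and 85%. This stands as a partial offset. It is idealised, r is not documented, and it does not show that 92% is met.

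**The clusters are idealised.** Nine is the stated group size. The article does not say whether places were refilled during the intake from March 2009 to July 2012. This also stands. At ICC .01 without loss the fall is only about 1 point, or about 4 points with few-group degrees of freedom.

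**Conclusion.** The point holds in a limited form, with medium confidence. The arithmetic behind the 92% is correct. What fails is its unstated premise of 54+54 independent, complete observations, which does not fit the group delivery and equal randomisation target given in the same article. The direction is certain for any positive ICC or any loss, other things equal. The size is not: 92% down to about 74%, or about 68% with few-group degrees of freedom, rests on assumed ICC, loss and stable groups, before any gain from partial data or baseline adjustment. The type I error of about 6–10% applies only if no therapy-group term is fitted. The article does not support concluding that the primary analysis is invalid, or that more patients should have been recruited.

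**What to change.** Keep the sample size; inclusion closed in July 2012.

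1. Restate the power at d = .65 as a range over group ICC and loss by 18 months, using the numbers actually randomised. State the independence and completeness assumptions behind the 92%.
2. In the primary growth model, name a random effect for therapy group that applies to the MBT-DH arm only, with small-sample degrees of freedom. Fix this before the last follow-up in July 2015. If the analysis plan already has such a term, a cross-reference is enough.

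The cost is wording, a lower stated power and wider intervals. With only six groups the widening may not be trivial. Each MBT-DH patient's group must be retrieved from the two sites, including any change of membership during intake.
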